## Abstract

**Introduction::**

Volume overload and the renin–aldosterone–angiotensin system (RAAS) are 2 major factors contributing to hypertension (HTN) among hemodialysis (HD) patients. Although volume-dependent components of HTN can be corrected by appropriate volume removal, a proportion of HD patients experience elevated blood pressure (BP) despite achieving euvolemic and ideal dry weight.

**Method and analysis::**

A single center, prospective, randomized, parallel design, single-blind trial will be conducted in the Malaysian state of Kelantan among postdialysis euvolemic hypertensive patients that are on regular dialysis at least 3 times a week. The primary outcome of the trial will be to note the effectiveness of losartan (RAAS inhibitor) in reducing systolic BP < 140 mm Hg compared to standard non-RAAS-inhibitor antihypertensive therapy. The secondary outcome will be to look at all causes of mortality. A body composition monitor (BCM) will be used to assess postdialysis volume and dry weight. Postdialysis euvolemic patients that have systolic BP > 140 mm Hg will be randomized using Covariate Adaptive Randomization to standard or treatment arm. Participants in the treatment arm will be given 50 mg of losartan once daily except on dialysis days, whereas the standard arm patients will be prescribed non-RAAS antihypertensive agents. The study participants will be followed for a period of 12 months. A Wilcoxon statistical test will be performed to note the difference in BP from baseline up to 12 months using Statistical Package for the Social Sciences (SPSS) 20.

**Ethical and trial registration::**

The study protocols are approved from the Ethical and Research Committee of the Universiti Sains Malaysia (USM/JEPeM/15050173). The trial is registered under the Australia New Zealand Clinical Trial Registry (ACTRN12615001322527). The trial was registered on 2/12/2015 and the 1st patient was enrolled on 10/12/2015. The trial was formally initiated on 16/02/2016.

**Conclusion::**

Management of HTN among HD patients requires understanding the primary cause of HTN and treating accordingly. The current trial is an attempt to reduce BP among postdialysis euvolemic but hypertensive patients.

## Introduction

1

Chronic kidney disease (CKD) has long been identified as a risk factor for cardiovascular disease and other complications, whereas the number of kidney failure patients treated with hemodialysis (HD) has drastically increased in the last decade. In 2009, more than 570,000 people in the United States were classified as having end-stage renal disease (ESRD), including nearly 400,000 dialysis patients and over 17,000 transplant recipients.^[1,2]^ The rise in incidence of ESRD is attributed to an aging populace and increases in hypertension (HTN), diabetes, and obesity within the US population.^[3]^

In Malaysia, the 21st Report of the Malaysian Dialysis and Transplant Registry 2013 stated that 5491 new HD cases were registered, representing an acceptance rate of 15 per million, while new peritoneal dialysis cases totaled 731, representing an acceptance rate of 25 per million. The total number of HD and peritoneal dialysis patients in 2013 increased to 28,822 and 2815, respectively. Geographically, the dialysis rate exceeded 100 per million for all states in Malaysia in 2013 with the highest rates reported in Pulau Pinang (303 pmp) and the lowest in Perlis (104 pmp). Over the last 10 years, the ratio of male to female incident and prevalent dialysis patients has remained the same, at about 55:45.^[4]^

Up to 90% of hemodialysis patients are hypertensive. Studies aimed at elucidating the pathophysiology of HTN HD patients concluded that 90% of cases resulted from sodium and volume overload (volume-dependent), while the majority of the remaining had elevated renin activity (renin-dependent), resulting in high blood pressure (BP) during HD.^[5]^ The renin–angiotensin–aldosterone system (RAAS) is a signaling pathway responsible for regulating the body's BP. Stimulated by low BP or certain nerve impulses, the kidneys release an enzyme called renin that undergoes various transformations, finally resulting in angiotensin II,^[6]^ which not only causes blood vessels to narrow (vasoconstriction), but also simultaneously stimulates the secretion of vasopressin (also called AVP). In this way, the overall volume of blood in the body is increased: more blood is pumped through constricted arteries, which increases the pressure exerted on the artery walls – so increasing the BP. Interestingly, the RAAS is activated in HD patients by the fact that renin is increased with HD ultrafiltration leading to HTN.^[7]^

Adequate extracellular volume control remains one of the principle goals for renal replacement therapies. Fluid balance is an integral part of HD to prevent under- or overhydration at the end of HD session, both of which are associated with cardiovascular and other complications.^[8]^ Hence, the correct quantification of extracellular fluid is essential for HD patients. A bioimpedence spectroscopy (a body composition monitor [BCM] manufactured by Fresenius Medical Care) allows quantification of extracellular fluid by comparison with a healthy population. A number of studies indicate that a BCM is an objective and reliable tool to assess the clinical dry weight and estimate extracellular fluid.^[9–12]^

The activation of the RAAS leads to narrowing of the lumen of blood vessels thus leading to a rise in BP even if the patient is euvolemic. Considering the importance of the RAAS in euvolemic hypertensive patients, the role of drugs blocking the RAAS needs further investigation.

### Rationale of this study

1.1

In the past, emphasis has often been placed on overall BP reduction of among HD patients. However, a “one-size-fits-all” approach for BP management may not be appropriate for all the patients on HD.^[13]^ The renin angiotensin system is activated in HD patients by the fact that renin is increased with HD ultrafiltration, leading to HTN. This makes the RAAS a potential target for antihypertensive drugs.^[14]^ Normally, volume overload and elevated BP suppress the renin system. Since this feedback mechanism is incomplete in CKD patients, they often have high BP with normal or elevated renin levels.^[15]^ Literature suggests that renin levels may be twice as high in hypertensive HD patients compared to normal, with a study reporting plasma renin activity increasing from 2.3 ± 0.5 ng/mL/h just before the initiation of HD to 6.5 ± 1.3 ng/mL/h over an 8- to 10-year period among hypertensive HD patients.^[15,16]^ This finding suggests that renin secretion continues even after complete decline of kidney function.

Fluid balance is an integral part of HD, and problems with it are associated with cardiovascular and other complications.^[17]^ The majority of fluid removal and maintaining an ideal hydration status is looked at by considering a patient's dry weight. However, dry weight is clinically determined by the lowest weight a patient can tolerate without intradialytic symptoms and hypotension in the absence of fluid overload. A bioimpedence device such as a BCM allows quantification of excess extracellular volume by comparison with a healthy population, thereby providing us with a more reliable measure of dry weight and patient hydration status.^[18]^ Importantly, volume-dependent components of HTN can be corrected by appropriate volume removal, though a proportion of HD patients experience elevated BP despite achieving euvolemic and ideal dry weight.^[19]^

Since there is a constant volume variation during HD sessions, there is a strong possibility that the RAAS will be activated, thereby making these patients a potential target of drugs blocking the RAAS. Hence, the current study is based on role of angiotensin receptor blockers (ARBs) in managing HTN among euvolemic HD patients.

### Rationale for intervention

1.2

ARBs and angiotensin-converting enzyme inhibitors are similar and both are often used during clinical practice for ESRD patients. An observational study suggests that an ARB in combination with another antihypertensive medication (but not an angiotensin-converting enzyme inhibitor) may have a beneficial effect on cardiovascular mortality among ESRD patients on dialysis.^[20,21]^ Based on cost-effectiveness and availability, and the opinion of a panel of experts, a decision was taken to use an ARB (losartan) for the intervention group.

## Method

2

### Trial design

2.1

The current study will be a single-center, prospective, randomized, parallel-design, single-blind trial that would be conducted in the Malaysian state of Kelantan at a CKD resource center of the Hospital Universiti Sains Malaysia (HUSM) and its associated dialysis centers. The study protocols are approved by the Ethical and Research Committee of Universiti Sains Malaysia (USM/JEPeM/15050173), and the trial is registered under Australia New Zealand Clinical Trial Registry (ACTRN12615001322527). The study purpose will be explained, and patients’ consent will be obtained before enrolling by the principle investigator.

### Eligibility criteria

2.2

Euvolemic patients with a postdialysis BP of more than 140/90 mm Hg will be included in the study. On the basis of expert opinion from nephrologists, patients aged between 30 and 80 will be included. The other eligibility criteria are: patients undergoing dialysis for at least 12 months, 2 to 3 HD sessions per week, and willingness to participate.

### Exclusion criteria

2.3

The exclusion criteria are as follows: patients with amputations; patients with neoplasm; patients with cystic kidneys; patients unwilling to participate in the study; patients already on ARBs; and patients with symptomatic hypotension or systolic BP less than 110 mm Hg.

### Prescreening

2.4

The current trial is a 2-phase study. Phase 1 is the prescreening procedure, including prospectively assessing the hydration status of hypertensive patients undergoing HD. After assessing the dry weight with a BCM, all efforts will be made to ensure the patient achieves the same dry weight at the end of their dialysis sessions. Patients that are still hypertensive (>140 mm Hg) 30 minutes after the dialysis sessions will undergo a volume assessment with a BCM device.

Patients that will be assessed as euvolemic by a BCM in 3 consecutive dialysis sessions but are still hypertensive (>140/90 mm Hg) despite achieving dry weight will be included in the trial. Since the purpose of phase 1 is to identify the euvolemic hypertensive population, it will be these patients that will be asked to join a randomized control trial (phase 2). A regular BCM assessment for dry weight will be done to ensure patients attain their specific dry weight and euvolemic states.

### Randomization of participants

2.5

Covariate adaptive randomization will be used to assign all prescreened participants that agree to participate in the study to the treatment or standard arm. Covariate adaptive randomization has an advantage over other randomization techniques in that it is able to achieve balance over a large number of covariates when the sample size is small to medium.^[22]^ The Taves covariate adaptive randomization method will be used for randomization to allow for the examination of previous participant group assignments in order to make a case-by-case decision on group assignment for each individual who enrol in the study. Using covariate adaptive randomization, patients will be assigned to the treatment or control arm. Based on expert opinion and preexisting literature, the covariates considered for this study will be: age, gender, diabetes, and year of dialysis. In order to avoid bias, randomization will be done by a computer programme, hence minimizing the risk of selection biasness and avoiding any influence of the researcher, the prescriber, or the participant on selection of group or medication. It is important to mention however that Scott et al^[23]^ argued that predictability and bias of randomization is true for all methods and so should not be overly penalized.

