### Standard and intervention arms

2.7

Both the standard and intervention arms will be randomized with equal numbers of patients. The standard-arm patients will receive antihypertensive therapy except RAAS inhibitors that included calcium-channel blockers, diuretics, alpha- and beta-blockers, whereas the intervention-arm patients will be prescribed ARB (losartan) alone or in combination with standard antihypertensive pharmacotherapy. In both study arms, patients will be allowed multiple antihypertensive pharmacotherapies to control BP, after discussion with a panel of experts. However, this will only be done where entirely necessary to avoid any deterioration to a patient's health. Finally, study intervention (losartan) and antihypertensive medication will be given to the patients on a weekly basis by the principle investigator. A member of patient's family will be consented to monitor a patient's adherence at home whereas a pill check will be performed once a week. Only the study participants will be blinded during the course of study.

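### Taves minimisation is specified with no random element, so an unblinded investigator who enrols and dispenses can predict much of the allocation (about 70% to 92% correct guesses, depending on what is known)

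*Protocol article*

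**What the plan says.** Protocol article, section 2.5 (Randomization of participants):

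- The method is named: "The Taves covariate adaptive randomization method will be used for randomization to allow for the examination of previous participant group assignments", and this is done "in order to make a case-by-case decision on group assignment for each individual who enrol in the study".
- The factors are listed: "the covariates considered for this study will be: age, gender, diabetes, and year of dialysis". No categories are given for age or years on dialysis.
- The safeguard offered is that "randomization will be done by a computer programme, hence minimizing the risk of selection biasness". The same sentence claims that influence by the researcher, prescriber or participant is thereby avoided.
- Predictability is then set aside by citing a published argument that "predictability and bias of randomization is true for all methods and so should not be overly penalized".

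No probability below 1 for the balancing arm is stated.

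Other sections show who knows what:

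- Section 2.1 (Trial design): "consent will be obtained before enrolling by the principle investigator".
- Section 2.7 (Standard and intervention arms): the principal investigator hands out losartan and the other antihypertensives every week, and "Only the study participants will be blinded during the course of study".
- Section 2.10 (Data handling and record keeping): the principal investigator collects all data and keeps the forms and patient logbooks.

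**The concern.** Taves minimisation gives the next patient to the arm with the smaller total over that patient's factor levels. Without a random element, chance enters only when the totals tie. Anyone who knows the earlier patients' arms and covariates can repeat the tally before approaching the next candidate.

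The article puts the necessary knowledge with one person. Whoever dispenses losartan to one arm and other drugs to the other knows the arms, and whoever collects the data knows the covariates. Candidates are also known in advance, because the prescreening phase (section 2.4) assesses them before they are asked to join.

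What is at stake is selection bias at entry. If the next arm can be guessed, the choice of whom to approach, when, and how persuasively can depend on it. Minimisation balances the four listed factors, and section 2.13 plans adjustment for the same four. Baseline blood pressure is not among them, although the primary end point in section 2.8 is a postdialysis blood pressure threshold. An imbalance created this way would be neither prevented by the allocation rule nor removed by that adjustment.

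**Working it through.** **Plan's own figure.** The article gives no figure for predictability. Its total sample size is used here only as the length of the allocation sequence: 70 × 1.25 = 87.5, rounded up to 88, as stated in section 2.12.

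**Inputs from the article.** Two arms with equal numbers, four factors, 88 patients, Taves rule, no stated random element.

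**Assumptions.** Age and years on dialysis have no stated categories. Sets of 2×2×2×2, 3×2×2×3 and 5×2×2×4 levels (age × sex × diabetes × years on dialysis) were tried. Ties are settled by a fair coin.

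**Rule simulated.** For a new patient with level l(k) on factor k, let S(A) and S(B) be the sums over the four factors of earlier patients in arm A and arm B who share level l(k). Assign the arm with the smaller sum. Each setting was run 1,500 times.

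**Fully informed guesser (knows earlier arms, covariates and cut-points).** The guess is right for every forced allocation and for half of the ties:

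correct = forced + 0.5 × (1 − forced)

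- 2×2×2×2: 0.840 + 0.5 × 0.160 = 0.920
- 3×2×2×3: 0.835 + 0.5 × 0.165 = 0.918
- 5×2×2×4: 0.832 + 0.5 × 0.168 = 0.916

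The simulated success rates agree (0.919, 0.917, 0.916). Of 88 allocations, about 74 are forced (0.84 × 88) and about 14 are ties. The number of levels hardly matters.

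**Less informed guesser, same rule, n = 88.**

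| Information used | Correct guesses |
|---|---|
| Sex and diabetes only (no cut-points needed) | about 77% to 79% |
| Running arm totals only | about 70% to 72% |
| All four factors, but wrong cut-points | about 68% to 72% |
| Simple randomisation, any information | 50% |

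**With a random element (balancing arm chosen with probability 0.8).**

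correct = 0.8 × (non-tied) + 0.5 × (tied)

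- 2×2×2×2: 0.8 × 0.888 + 0.5 × 0.112 = 0.766
- 5×2×2×4: 0.8 × 0.879 + 0.5 × 0.121 = 0.764

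So the fully informed guesser falls from about 92% to about 76% to 77%, and no allocation is certain. A guesser who tallies only sex and diabetes falls to about 67%. With probability 0.7 the fully informed figure is about 68%.

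**Price in balance.** At n = 88 the mean absolute difference in arm size rises from about 0.3 to about 1.0 with two-level factors, and from about 0.5 to about 1.2 with the finest categories tried.

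**The case against.** - **The 92% is an upper bound.** It needs the programme's cut-points for age and years on dialysis, and no section says that the investigator has them. This stands, and it is why a range is given. It does not remove the concern, because sex and diabetes alone, or bare arm totals, still give guesses well above 50%.
- **The article does not say that the investigator holds the allocation list.** Correct. Section 2.10 mentions data forms, incidence reports and logbooks only. Knowledge of earlier arms is inferred from weekly dispensing without blinding. The inference is a strong one, but it is an inference.
- **Entry is constrained.** Section 2.4 requires euvolemia in three consecutive sessions and a blood pressure threshold, and section 2.5 applies allocation to prescreened patients who agree. So allocation already follows agreement, which leaves timing and persuasion as the main routes. These are narrower than free choice of patient, but real.
- **The full protocol may add a random element or an independent operator.** It may, and it is not shown. But the article does more than stay silent: it names the method, asserts that influence is avoided, and argues predictability away.
- **The fix is partial.** Agreed. With 0.8 a fully informed guesser is still right about 77% of the time, and one person still enrols and dispenses.

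A reader might go further and infer that the missing chance element undermines the significance tests. The documents do not support that: about one allocation in six is still random, and adjustment for all four factors is planned. Nor can the cited argument on predictability be called wrong, since its source is not at hand. What can be said is that it protects nothing in this trial.

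**Conclusion.** The concern holds as a stated weakness of the design. Without a random element, about five in six allocations are determined by earlier assignments and the new patient's covariates. An unblinded investigator who dispenses could guess the next arm correctly about 70% to 92% of the time, depending on whether the cut-points are known. The claim that researcher influence is avoided therefore does not hold as written: a computer programme stops a person from picking the arm, not from picking the patient or the moment.

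A reader might conclude that the next arm is nearly always known, or that selection has in fact been biased. Neither follows. About one allocation in six is a tie, the top figure rests on cut-points that the article does not give, and nothing shows that anyone used the information. The result also assumes coin-settled ties and that the full protocol adds no random element.

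**What to change.** Amend section 2.5 for all patients still to be enrolled:

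1. Use minimisation with a random element: the programme assigns the arm that reduces imbalance with a stated probability below 1. A value of 0.8 is one conventional choice.
2. Release each assignment only after the patient has consented and been irrevocably entered.
3. Replace the sentence that sets predictability aside with a description of these safeguards.

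If the full protocol already contains such a step, the article should state it instead.

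**Cost.** Balance becomes slightly looser, with a mean arm-size difference of about 1 patient instead of about 0.3; the planned adjustment covers the four factors. The abstract gives the first enrolment as 10/12/2015 and formal initiation as 16/02/2016, so this is an amendment to a running trial and not only a change of setting. The documents do not show whether the existing programme offers such a parameter. Patients already allocated stay under the old rule, and this should be reported as a limitation. Predictability is reduced, not eliminated.

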### Washout period

2.6

The purpose of the washout period is to eliminate previously given hypertensive medication. Since all enrolled patients will be hypertensive, care has to be taken not to deprive patients of antihypertensive therapy. During the washout period patients, in consultation with a cardiologist and a nephrologist, will be maintained on other hypertensive medication (except RAAS inhibitors) to maintain their BP and to avoid any bias in the study. On the completion of the washout period, the patients will enter the regular trial phase.

### Standard and intervention arms

2.7

Both the standard and intervention arms will be randomized with equal numbers of patients. The standard-arm patients will receive antihypertensive therapy except RAAS inhibitors that included calcium-channel blockers, diuretics, alpha- and beta-blockers, whereas the intervention-arm patients will be prescribed ARB (losartan) alone or in combination with standard antihypertensive pharmacotherapy. In both study arms, patients will be allowed multiple antihypertensive pharmacotherapies to control BP, after discussion with a panel of experts. However, this will only be done where entirely necessary to avoid any deterioration to a patient's health. Finally, study intervention (losartan) and antihypertensive medication will be given to the patients on a weekly basis by the principle investigator. A member of patient's family will be consented to monitor a patient's adherence at home whereas a pill check will be performed once a week. Only the study participants will be blinded during the course of study.

### Study end point

2.8

A medication dose of 50 mg losartan per day for 3 weeks will be initiated as a test dose to note any incidence of hypotension. If there is no hypotensive event, patients will continue with 50 mg daily every day except dialysis days. The dose could be a titrated dose up to 100 mg/day, depending upon expert opinion and clinical scenario. As for treatment group, the dose titration would be initiated with losartan 50 to 100 mg followed by non-RAAS antihypertensive agents. As for standard group, the choice of dose titration would be left to expert opinion. The primary end point will be achieved by having a postdialysis BP of <140/90 mm Hg and maintaining this for 4 weeks. The secondary end point will be looking at all causes of mortality.

